**Fig. 1 Fig1:**
[figure not shown]
Study flow chart

#### Assessment and allocation to the intervention

Participants are randomised to the conditions through a computer-generated algorithm created by Unipark. The allocation sequence is concealed to the researchers until interventions are assigned. For each measurement timepoint, participants receive an individual link via email that invites them to complete the online questionnaires at Unipark. Participants in the intervention group receive a personalized reminder 2 weeks after their vacation via email, asking them to complete the final questionnaire. All study-related information will be stored securely at the study site and handled with great care. Data are recorded and evaluated pseudonymised and transmitted in encrypted form. Data are stored on the server of Leuphana University in Lueneburg. Neither personal photos nor the content of notes in the app is transmitted or analysed. Only the amount of Dailys will be recorded for each participant.

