## Methods

### Study design

For a proof of concept study and employing a pre-post-design, our research team has investigated the feasibility of use of the app-based intervention “Holidaily 1.0.” amongst workers (*N* = 77) [58]. Holidaily is a low-intensity, gamified, smartphone-based intervention. The app provides users with three suggestions promoting recovery behaviour daily. In this study, the intervention was begun 2 weeks prior to each worker’s vacation and continued beyond their return to daily working life. Initial findings were promising, as workers reported a significant improvement from 2 weeks before to 2 weeks after their vacation, and exhibited reduced work-related rumination during their leisure time, with an effect size of *d* = 0.68. To date, research indicates that, with no intervention, mental health variables resume baseline scores within 2 weeks after a vacation has ended [47]. Our next step is to establish whether meaningful effects can also be detected when an intervention and control group are compared.

Therefore, the current two-armed randomised controlled trial is being conducted to evaluate the efficacy of the app-based intervention “Holidaily 2.0” relative to a waitlist-control group (CG). All participants are invited via email to complete online questionnaires 2 weeks prior to their vacation, on their last working day, in the middle of their vacation, at the end of their first day working post-vacation, and 2 weeks after their vacation has ended (see Table 1). The intervention group receives an additional questionnaire 4 weeks after their vacation (extended follow-up). On average, these assessments last 15–30 min each. After the CG complete their final questionnaire, 2 weeks after their vacation, they receive an automated code via Email which allows them to immediately access Holidaily.

**Table 1 Tab1:** Overview of variables and measuring time points

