#### Waitlist-control group

Participants in the waitlist-control group (CG) are invited to answer the same questionnaires following the same timeframe as the IG. However, subjects in the CG only receives access to Holidaily 2 weeks after they have returned to work. Controls can, therefore, use Holidaily during their subsequent daily working life and next vacation.

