### Primary analysis

The primary analysis will evaluate the efficacy of Holidaily. The primary endpoint is the difference in work-related rumination, assessed using the irritation score, between the IG and CG 2 weeks after the vacation. We will use analysis of covariance (ANCOVA) to investigate differences in the primary outcome between the two groups, as simulation studies have demonstrated that ANCOVA is the most robust method for analysing RCT’s, in terms of protecting against bias, while enhancing precision and statistical power [117, 118]. Baseline scores for the primary outcome will be included as a covariate. In addition, for the analyses of differences in work-related rumination at the end of the last work day, mid-vacation and at the end of the first work day Bonferroni-Holm corrections will be used to reduce the chances of chance capitalisation [119].

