### Sensitivity analyses

To assess the robustness of these results, sensitivity analyses will be conducted. First, a separate analysis will be performed for participants who complete the main assessment 2 weeks after vacation (study completer sample). Second, all participants that used the app at least three times per week will be analysed (per protocol sample). Third, to account for potential baseline differences, despite randomisation, we will include all continuous variables with a between group difference of *d* = 0.20 or more and each categorical variable with 10% difference or more as covariates.

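### As written, the reminder for the primary-endpoint questionnaire goes to the intervention group alone, so the two arms reach that assessment by different follow-up procedures

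*Protocol article*

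**What the plan says.** All quotes are from the protocol article.

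- Assessment and allocation to the intervention, on invitations for everyone: "For each measurement timepoint, participants receive an individual link via email that invites them to complete the online questionnaires at Unipark".
- The same section, on reminders: "Participants in the intervention group receive a personalized reminder 2 weeks after their vacation via email, asking them to complete the final questionnaire".
- Primary analysis: "The primary endpoint is the difference in work-related rumination, assessed using the irritation score, between the IG and CG 2 weeks after the vacation".
- Study design, on the control group: "After the CG complete their final questionnaire, 2 weeks after their vacation, they receive an automated code via Email which allows them to immediately access" the app. The same section, on the intervention group: "The intervention group receives an additional questionnaire 4 weeks after their vacation (extended follow-up").
- Waitlist-control group: its members are invited to "answer the same questionnaires following the same timeframe as the IG". No reminder is mentioned there or elsewhere for this arm.
- Statistical analyses and Sensitivity analyses: intention-to-treat with multiple imputation, a baseline-adjusted ANCOVA, and three sensitivity analyses. The first of these is on completers: "a separate analysis will be performed for participants who complete the main assessment 2 weeks after vacation (study completer sample").

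**The concern.** The primary outcome is an online self-report, so it exists only for people who answer. The text moves from participants in general, who all get a link, to the intervention group, which also gets a personalised reminder. The stated time of that reminder is the time of the primary endpoint. The control group has an inducement of another kind: app access once T5 is done.

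If this is how the trial runs, the people who answer T5 are brought in by different means in each arm. Those who respond only because they were reminded would be observed in the intervention group and missing in the control group. Those who respond in order to get the app would be observed in the control group and have no counterpart in the intervention group. Randomisation balances the arms at baseline but does not protect the comparison of responders. The completer analysis is directly exposed. The imputed analysis is exposed as far as response still depends on T5 rumination once the observed data are taken into account. The trial is sized for d = 0.20, so a small distortion counts.

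**Working it through.** **The plan's own figure.** Sample size calculation gives d = 0.20, two-sided 5% and 80% power, with N = 788. An exact two-sample t-test gives 393.4, rounded up to 394 per arm, hence 2 × 394 = 788. The figure reproduces and is not in dispute.

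**Which questionnaire is meant?**

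| Clue | Points to |
|---|---|
| The reminder is sent 2 weeks after the vacation | T5 |
| Study design calls the control group's 2-week questionnaire its final one | T5 |
| The intervention group's last questionnaire is at 4 weeks, in that arm only | T6 |
| Limitations describes the extended follow-up as lasting 2 weeks | T6, by a possible slip |

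T5 is the natural reading, but the two sections do not fully agree.

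**What could it be worth if T5 is meant?** The article gives no response rates, so these inputs are assumptions:

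- rI and rC: T5 response in the intervention and control groups
- k: the gap in rumination, in SD, between the extra responders gained by the reminder and the other intervention-group responders, taken as 0.2 to 0.5

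Shift in the observed intervention-group mean = (rI − rC) / rI × k.

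| rI vs rC | Share of extra responders | Shift, k = 0.2 | Shift, k = 0.5 | Share of d = 0.20 |
|---|---|---|---|---|
| 80% vs 75% | 0.05/0.80 = 0.0625 | 0.013 SD | 0.031 SD | 6% to 16% |
| 80% vs 70% | 0.10/0.80 = 0.125 | 0.025 SD | 0.063 SD | 13% to 31% |
| 80% vs 65% | 0.15/0.80 = 0.1875 | 0.038 SD | 0.094 SD | 19% to 47% |

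**Effect on the test.** With 394 randomised per arm, nI = 394 × rI and nC = 394 × rC. The test statistic moves by shift / √(1/nI + 1/nC). For 80% vs 70% and k = 0.5, this is 0.0625 / √(1/315.2 + 1/275.8) = 0.0625 / 0.0825 = 0.76. The two-sided error rate when there is no true effect becomes 11.8% instead of 5%. At k = 0.2 it is 6.1%. For 80% vs 75% it is 5.3% to 6.7%.

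**Limits of these figures.** They describe a comparison of responders only, not the planned primary analysis. Table 1 shows the same rumination scale at T1 to T4 in both arms. Imputation that uses those scores would remove the part of the gap that they explain. With equal response and the same response mechanism in both arms, the shift is zero.

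**The case against.** The strongest reply is that this is one loosely worded sentence in a condensed article. No sentence denies the control group a reminder, and reminder schedules are often left to the full protocol. If the sentence was meant for T6, naming the intervention group alone is natural and the problem at the primary endpoint disappears. This stands as a reason to clarify first. It does not dispose of the point, because the text makes a positive statement about one arm at the primary timepoint.

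A reader might go further and infer that differential response is built into the primary outcome. The documents do not support that. The access code may raise control-group response as much as the reminder raises response in the other arm, so the net gap in numbers could be near zero. Equal numbers would still not make the responders alike, since the inducements differ.

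A reader might also infer a known direction, for instance that heavy ruminators answer only when reminded. Nothing in the article shows this. If it were so, the reminder would raise the intervention-group mean and work against the app. If the extra responders ruminate less, the bias would favour the app.

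Finally, a reader might take the 0.01 to 0.09 SD as the bias in the primary result. It is a raw shift among responders on assumed inputs, before imputation and ANCOVA. That the article lists no analysis relaxing missing-at-random is not a fault in itself, since such analyses commonly sit in an analysis plan, which is not shown here.

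**Conclusion.** The point holds in a limited form. As written, the article gives the arms different follow-up procedures at the primary endpoint: a reminder in one, and an access code on completion in the other. This can make response differ by arm in a way that matters for a target of d = 0.20. That only the intervention group is reminded is inferred from the wording, and the wording conflicts with that group having a later questionnaire. Study design and Assessment and allocation to the intervention must therefore be reconciled.

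The size and sign of any bias are unknown. The complete-case range of about 0.01 to 0.09 SD (6% to 47% of d = 0.20) rests entirely on assumed response gaps of 5 to 15 points and assumed differences of 0.2 to 0.5 SD. The shift should be less after imputation that uses the T1 to T4 rumination scores. The case for acting is that the remedy is cheap and removes an avoidable source of bias in the only outcome on which the article intends to draw a strong conclusion.

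**What to change.** 1. Establish what is done. If the sentence refers to T6, or if both arms already receive the T5 reminder, correct the sentence so that it agrees with Study design.
2. Otherwise, send the identical T5 reminder (same text, timing and number) to both arms for all remaining participants. Procedures has recruitment running until about winter 2021, so the rule can still be changed for those not yet at T5.
3. Report T5 response by arm in any case.
4. If participants were already followed under the unequal rule, add one delta-adjusted multiple-imputation sensitivity analysis. Vary the shift in imputed T5 rumination separately in each arm and in both directions, for example up to 0.5 SD (the top of the range assumed above), and report where the primary conclusion changes. Shifting the intervention group alone would not do, because people reachable only by a reminder remain missing in the control group.

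The cost is one email rule in the survey platform, one corrected sentence and, if step 4 applies, one extra imputation run. The sample size of 788 does not change.

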#### Sample size calculation

Sample size calculation was based on the expected standardized difference in the primary outcome measure — work-related rumination (Irritation Scale, [76]) — between the intervention and control groups 2 weeks post vacation. Evidence from meta-analyses and systematic reviews on the efficacy of digital interventions for mental health, and specifically stress management, in workers indicate an effect size of ﻿*g* = 0.54 [77]. More precisely, data on mental health apps as a standalone treatment for clinical samples targeting various conditions yield mixed results: for instance, a significant effect for depression ﻿*g* = 0.33, but no effect for ﻿anxiety [70]. Few RCTs indicate the potential of any app-based intervention targeting stress-related complaints amongst workers [65, 66, 74]. Though clear results concerning the efficacy of app-based interventions cannot be drawn, findings nonetheless indicate their potential. From a public health perspective, the aim is to reach the whole population. As such, smaller effects are meaningful, as more people can potentially benefit from an intervention. Taking these two lines of reasoning together, we regard an effect of *d =* 0.20 for work-related rumination as meaningful, especially when considering that the app constitutes a low-intensity self-help intervention for the general working population. A priori G*Power analysis [78] for a two-tailed test, in which 80% power and a 5% significance level are assumed, indicates that an overall sample size of *N* = 788 is needed to detect differences statistically.

### Intervention content and app design

The Holidaily app is a stand-alone program for mobile devices with either Android or iOS operating systems. Holidaily is available in German, Finish and English and was developed along several lines of research. Its key components are prompts for recreational activities, called “Dailys”. Dailys are based on behavioural activation strategies and refer to specific activities that positively influence mental health [79]. To promote behavioural change, appropriate behaviour-change techniques — like health-development tracking and prompts — were included [80]. An important element of the gamified app is its potential to reward participants by enabling the collection of points in exchange for completing Dailys and tracking one’s wellbeing (for examples, see Additional file 1).

#### Holidaily’s key features

The Holidaily-app consists of five sections (for examples, see Additional file 2). First, on the “***Home***” screen, users can keep track of their collected points and navigate directly to “Dailys”. The more points the user collects, the “richer” the background of the home screen appears. The avatar on the home screen also reflects whether users are on vacation or not. This is indicated by the avatar either holding a cup of coffee and wearing a business-like outfit, representing daily working life, or holding a cocktail and wearing a flower chain and hula skirt to indicate that they are on vacation.

The second section consists of “***Dailys***”. This is the main section, with each Daily corresponding to at least one of the six mechanisms of the DRAMMA model [36]. The various exercises differ before, during, and after vacation. Dailys foster each mechanism to a different degree of intensity, duration and effort. This section consists of three features: (i) Users choose and “book” one Daily from three suggestions or, alternatively, generate their own recovery activity. Users can also place Dailys “on hold” to be carried out at a more convenient time. (ii) After the user completes the respective exercise, they are asked to rate it, based upon the six DRAMMA recovery experiences. Users rate the extent to which the Daily helped to foster the experiences of detachment, relaxation, autonomy, mastery, meaning and affiliation. The mean score of the user’s rating is displayed graphically in the third section, called “***Recovery***”. Encouraging users to rate their recovery experience fosters reflection over which particular activity was helpful for the individual’s recovery experience, while also encouraging perceived recovery self-efficacy. As a reward, users receive points for each completed Daily; (iii) users are presented with an overview of all “on hold”, “booked”, and “done” Dailys. The fourth section, “***Feel***”, invites users to rate their wellbeing using three validated, one-item questions regarding their experience of their past day, mood and energy level [81–83]. Users are encouraged to complete this section on a daily basis. The fifth section, “***Recovery***”, provides users with a summary of their recovery profile and has three sub-sections. Graphs visualize users’ recovery and wellbeing history, as well as their individual recovery strengths. This information is based on data entered by users. The section aims to promote users’ self-reflection, self-monitoring, and perceived self-efficacy.

#### Additional features

Holidaily offers additional features, like information about the vacation location, weather forecasts, a walkthrough, and a section with additional information about the app’s scientific background. Pictures can be uploaded to individualize Holidaily’s interface and keep track of the completed Dailys (i.e., users can upload a photo and write a short note about how they completed the Daily). The Daily overview can serve as a diary and users can always go back to view their completed Dailys.

#### Improving adherence to the intervention

Several steps have been taken to improve participants’ adherence to intervention protocols and reduce non-responses, as suggested by Newman [84] (Additional file 2). For example, Holidaily sends push-messages on a daily basis to remind users to complete Dailys and rate their wellbeing. To further foster engagement in recovery behaviour, participants can search for specific Dailys that were particularly helpful at promoting experiences of recovery via a sorting function within the app. Users also receive a weekly feedback email that summarises their recovery development.

#### User experience

As high user exposure rates are considered pivotal to an app’s effectiveness [85], aspects highlighted by the Mobile App Rating Scale (MARS: [86]) were considered when designing Holidaily. Special focus was given to attain good user experiences, as they are considered by MARS to be highly influential, in terms of determining the quality of the app promoting behavioural change [86]. More specifically, recent findings by this study team support this claim and that a user’s recovery seems to be uniquely predicted by the user’s experience with the app [58]. Furthermore, an app review that investigated the use of gamification techniques in stress management apps identified 17 commonly-used gamification features [87]. Of these 17 features, nine were considered during the designing of Holidaily (see Additional file 1). These, for instance, include the avatars called “Holidaisy” and “Holidave”, which reflect users’ wellbeing.

### Intervention

#### Holidaily-app intervention group

Participants in the Holidaily-app intervention group (IG) receive access to the Holidaily-training app 3 weeks before their vacation is due to start. After logging in, users create an individual profile for their upcoming vacation. This step includes entering the following data: vacation location, first and last day of work, and first and last day of vacation. Finally, users answer three questions related to each of the six DRAMMA dimensions. These questions will make it possible to compare their actual and desired levels of recovery experiences 2 weeks after returning from their vacation. After they have generated a personal vacation profile, users can start using the app, completing and keeping track of their Dailys and wellbeing.

#### Waitlist-control group

Participants in the waitlist-control group (CG) are invited to answer the same questionnaires following the same timeframe as the IG. However, subjects in the CG only receives access to Holidaily 2 weeks after they have returned to work. Controls can, therefore, use Holidaily during their subsequent daily working life and next vacation.

### Outcome measures & potential mediator and moderator

Work-related rumination after vacation is considered the primary outcome measure. Secondary outcome measures include mental health and work related health, and are only descriptive and non-explanatory in nature. Further variables not directly related to health, like personal and work characteristics, are defined as other variables. Table 1 provides an overview of all instruments applied at each measurement time point. Participants are asked to respond to all questions thinking about the previous week, unless otherwise clearly stated. All self-report measures are assessed in German.

#### Demographics

A self-designed questionnaire is used to collect general and vacation specific demographic data 2 weeks prior to the vacation; for instance, participant’s age, sex, relationship status, number of children, educational background, work status (part/fulltime), work hours per week per their contract, and actual working hours, length of employment, whether or not they have a managerial position, frequency working from home, last/first work day, and first/last vacation day.

#### Vacation specifics

Directly before participants leave for their vacation, they are asked to indicate their anticipated work accumulation during their absence (on a scale 1–5), type of vacation, who they are going on vacation with and how good their relationship is (on a scale 1–10), do they perceive they have control regarding the organisation of their vacation (on a scale 1–10), what is their vacation destination and have they been there before, and what are their expectations regarding their vacation. Further vacation specific questions are asked directly after their vacation, including did they enjoy their vacation (on a scale 1–10); what was the weather like; did they have negative/positive experiences during their vacation (open-ended question); how many hours did they work during their vacation; and, if so, did they enjoy it and experience control over their work (on a scale 1–5); what did their work involve; and to what extent and how often were participants contacted by colleagues, clients or superiors during their vacation.

